**Objectives:**

**Methods and analysis:**

This is a Canadian convergent parallel mixed-methods study. The quantitative strand uses a retrospective cohort design to assess birth group differences in rates of Tdap and COVID-19 vaccination, gestational diabetes screening, length of post-partum hospital stay, and onset of depression, anxiety, and adjustment disorder, using administrative data from ICES, formerly the Institute for Clinical Evaluative Sciences (Ontario) and PopulationData BC (PopData) (British Columbia). Differences by socioeconomic and ethnocultural status will also be examined. The qualitative strand employs qualitative description to interview people who gave birth between May 2020- December 2021 about their COVID-19 risk perception and health decision-making process. Data integration will occur during design and interpretation.

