## Objectives, questions and hypotheses

This research study has two objectives:

Evaluate potential associations between exposure(s) and outcome(s) for births occurring in 2019 (Jan 1 2019 –Mar 31 2019 births), 2021 (Jan 1 2021 –Mar 31 2021 births), and 2022 (Jan 1 2022- Mar 31 2022 births) birth groups in Ontario and BC related to vaccination, perinatal care, and mental health, overall, by race/ethnicity and by income. *(Quantitative strand)*Understand how people who gave birth in Ontario or BC in 2020 or 2021 perceived COVID-19 risk and how pandemic circumstances influenced their decision-making about key elements of pregnancy, including vaccination, perinatal care, social support and mental health. *(Qualitative strand)*

Research questions and hypotheses have been operationalized according to our three themes:

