### Quantitative analyses

#### Descriptive

The primary goal of the quantitative analysis is to describe and compare rates of our outcomes across birth groups to help explain the qualitative findings. Pregnancy-related factors will be reported using measures of general frequency (i.e., counts and proportions), central tendency (i.e., means and medians), and dispersion (i.e., standard derivations and interquartile range). We will examine maternal age, rurality, CIMD measures (i.e., ethnocultural composition, economic dependency, and residential instability), medical practice characteristics of the mother’s perinatal care provider, parity, mental health history (e.g., previous diagnoses or emergency department visits for mental health), the use of assistive fertility, delivery characteristics (e.g., gestation length and delivery type), and newborn outcomes (e.g., infant birth weight and neonatal intensive care unit admission). These factors were identified *a priori* based on a review of the literature and consultations with theme group experts.

Data will be examined for completeness, the presence of outliers, and the nature of the variable distribution for continuous variables (e.g., skew). We will report the completeness range for each exposure variable. Cases with missing data will be deleted within each analysis. Where data are incomplete for key variables, we will consider using multiple imputation.

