#### Inferential

The secondary analysis is to test for associations between our outcomes, primary exposure (birth group), and other covariates using multivariable logistic and linear regression. Covariates will be selected based on review of the literature, affirmed by topic and clinical experts. We will utilize logistic regression for our binary outcomes (i.e., vaccination status, gestational diabetes screening, and new onset of depression, anxiety, or adjustment disorder) and linear regression for our continuous outcome (i.e., postpartum length-of-stay). The best-subset approach will be used to identify the subset of covariates that best define the relationship with each outcome. This approach was selected to avoid suppressor effects commonly found with stepwise methods and statistically pre-determined predictors (e.g., *p* < 0.25). The Akaike information criterion (AIC) will be used to evaluate fit of the multivariable logistic regression models; R^2^ will be used to assess goodness of model fit for linear regression. We will verify model assumptions and employ methods such as robust variance estimation to address violations. We will also stratify these models by area-level information on socioeconomic status and ethnocultural composition to examine differences for low-income and racialized sub-groups.

All analyses will be performed using Statistical Analysis Software (SAS), version 9.4 (SAS Institute, Inc., Cary, North Carolina).

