## Strengths and limitations

This study has several strengths. The large administrative datasets offer significant statistical power to investigate changes in health care use, stratified by markers of socioeconomic and ethnocultural status. The cross-provincial nature of our analysis allows the observation of consistency or change based on different healthcare policies, vaccine availability, medical care provision, and COVID-19 burden. The integration with qualitative data offers the potential for explaining observed differences. Our study team incorporates multiple individuals with lived experience of a pandemic pregnancy, and frontline clinicians who cared for pregnant people in both provinces during the pandemic.

This study has some limitations. Relying on administrative data hinders the ability to gather some data points of interest. For example, neither ICES or PopData have patient-level demographic data about race or socioeconomic status. Instead, we will rely on area-level data abstracted from the 2016 Canadian Census, operationalized through the CIMD. The administrative datasets exclude some births, such as those which took place outside of a hospital setting. Qualitative data will be gathered from people who gave birth between May 1, 2020 to Dec 1, 2021, which may introduce some challenges with recall and social desirability bias. However, our co-investigators with lived experience assure us that due to the unique and challenging nature of these decisions, they are able to recall their decision-making very clearly.

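### Socioeconomic and ethnocultural differences are to be examined by stratified models alone, which do not estimate whether the birth-group effect differs between strata

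*Protocol article*

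**What the plan says.** Objective 1 (protocol article, Objectives, questions and hypotheses) asks for associations across the three birth groups "related to vaccination, perinatal care, and mental health, overall, by race/ethnicity and by income". The abstract adds: "Differences by socioeconomic and ethnocultural status will also be examined".

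Under Quantitative analyses, Descriptive, the aim is stated on the rate scale: "The primary goal of the quantitative analysis is to describe and compare rates of our outcomes across birth groups". Three measures of the Canadian Index of Multiple Deprivation (CIMD) are among the factors to be described: ethnocultural composition, economic dependency and residential instability.

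Under Inferential, regression is the secondary analysis. The text says "We will utilize logistic regression for our binary outcomes", gives postpartum length of stay a linear model, and sets covariate selection as follows: "The best-subset approach will be used to identify the subset of covariates that best define the relationship with each outcome". The section then gives its only inferential method for the equity question: "We will also stratify these models by area-level information on socioeconomic status and ethnocultural composition to examine differences for low-income and racialized sub-groups".

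The article states no birth group by stratum interaction, heterogeneity test or other contrast between strata. It names no absolute measure for the logistic models. It does not say whether best-subset selection is repeated within each stratum.

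**The concern.** The article's rationale is partly about change in disparity: the introduction to Theme 1 says that an overall rise in vaccination hides growing differences by ethnicity and income. The useful question is therefore whether the change between birth groups was larger in some strata than in others. Separate fits answer a different one, namely how large the change was inside each stratum.

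Two misreadings follow. First, with no contrast between strata, a reader is left to set p-values side by side, and one stratum can cross 0.05 while another does not for reasons of chance or stratum size. Second, for the binary outcomes the models yield odds ratios while the stated interest is in rates. Whether a gap in rates widened cannot be read from odds ratios alone when the strata start from different rates.

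The first problem affects every model, including the linear one for length of stay. The second affects only the binary outcomes.

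**Working it through.** **Inputs from the article.** Annual births are 140,000 (Ontario) and 42,000 (BC), over three January to March windows. The stated totals reproduce: 140,000 × 3 × 1/4 = 105,000 and 42,000 × 3 × 1/4 = 31,500, or 35,000 and 10,500 per birth group.

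**Assumptions, not in the shown text.** Five equal strata, so 7,000 (Ontario) and 2,100 (BC) per birth group per stratum; two-sided alpha 0.05; 80% power where a detectable effect is given; no covariates. All outcome rates below are illustrative, since S2 Table is not shown.

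**1. Discordant significance with no true difference.** If two independent strata have the same true effect and each has power π, the chance that exactly one is significant is 2π(1 − π):

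- π = 0.3: 2 × 0.3 × 0.7 = 0.42
- π = 0.5: 2 × 0.5 × 0.5 = 0.50
- π = 0.8: 2 × 0.8 × 0.2 = 0.32

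**2. A worked pair of BC strata, n = 2,100 per group.** SE(log OR) = √[1/(n p₁(1−p₁)) + 1/(n p₂(1−p₂))].

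- Stratum A, 30% to 26.2%: OR 0.83 (95% CI 0.72 to 0.95), p = 0.006.
- Stratum B, 30% to 28%: OR 0.91 (0.79 to 1.04), p = 0.15.
- Contrast A v B: ratio of ORs 0.828/0.907 = 0.91, z = −0.94, p = 0.35.
- On the rate scale: −3.8 − (−2.0) = −1.8 points, with SE √[(0.2100 + 0.1934 + 0.2100 + 0.2016)/2,100] = 1.97 points. The 95% CI is −1.8 ± 1.96 × 1.97, or −5.7 to 2.1 points.

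One stratum is clearly significant and the other is not, yet the data do not show that they differ.

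**3. Odds ratios against rate gaps.**

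| Starting rate | OR for a 10-point drop | Change in rate if OR = 0.6 |
|---|---|---|
| 90% | (0.8/0.2)/(0.9/0.1) = 0.44 | to 84.4%, −5.6 points |
| 80% | (0.7/0.3)/(0.8/0.2) = 0.58 | to 70.6%, −9.4 points |
| 50% | (0.4/0.6)/(0.5/0.5) = 0.67 | to 37.5%, −12.5 points |

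Take the 90% and 80% strata. With OR 0.6 in both, the ratio of ORs is 1, but the gap grows from 10.0 to 84.4 − 70.6 = 13.8 points. With a 10-point drop in both, the gap is unchanged, but the ratio of ORs is 0.444/0.583 = 0.76.

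**4. What separate fits can supply.** In simulated data with the same covariate in both strata, the difference in log ORs from two separate fits was 0.1041 (SE 0.0957, z = 1.09). The interaction term of the fully interacted pooled model was identical. The equality requires the same covariates in every stratum. Adjustment also moves an odds ratio by itself: at a 50% base rate, a conditional OR of 0.70 becomes a marginal OR of 0.71 to 0.81 as the standard deviation of an omitted predictor rises from 0.5 to 2.

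**5. Feasibility of the interaction.** The minimum detectable ratio of ORs between two strata is exp[(1.96 + 0.84) × √(2/(n p(1−p))) × √2]:

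| Base rate | Ontario | BC |
|---|---|---|
| 10% | 1.25 | 1.50 |
| 30% | 1.16 | 1.31 |
| 50% | 1.14 | 1.28 |
| 90% | 1.25 | 1.50 |

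**The case against.** Several stronger readings are tempting, and the documents do not support them.

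- *Odds ratios cannot be compared when base rates differ.* They can: a ratio of odds ratios is a valid multiplicative contrast, and step 4 shows it can be recovered from separate fits. What stands is narrower. The article does not say the contrast will be formed, it leaves open whether covariates would match across strata, and the ratio does not describe rate gaps.
- *The authors will judge disparity by comparing p-values.* The article nowhere says so. The risk is to the reader, because no contrast is stated.
- *Effect modification is a headline hypothesis.* Objective 1 asks for results overall and by sub-group, none of the six numbered hypotheses concerns a difference between strata, and the regressions are secondary. This limits the weight of the point. Even so, the sentence on stratification gives its purpose as examining differences.
- *Area-level results are passed off as individual ones.* The limit is disclosed: the article says "neither ICES or PopData have patient-level demographic data about race or socioeconomic status", and the stratification sentence itself says the information is area-level. This is not part of the point.

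Two further objections deserve an answer. Rates are to be described as the primary goal, so the odds ratios need not be the only evidence; but the text does not promise rates by stratum. An interaction test could also sit in an analysis plan that is not shown. That is fair, but the article does not leave the method open: it names stratification.

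Finally, discordant significance matters mainly for modest effects. A 10-point change would be detected in every stratum assumed here.

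**Conclusion.** The point holds in a limited form. The stated method yields birth-group effects within strata and no estimate or test of the difference between them, for the logistic and the linear models alike. Under equal true effects, two strata disagree on significance in 32% to 50% of cases across powers of 30% to 80%. For the binary outcomes, equal odds ratios can accompany a gap in rates that widens by 3.8 points, and unequal ones (ratio 0.76) a gap that does not change.

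These sizes are illustrative. They rest on assumed base rates, power and, in the BC example, five equal strata. The structural point, that stratified fits carry no contrast between strata, needs none of these. The planned analysis is not invalid: the stratified odds ratios remain correct for their own strata. The change is worth making because it needs no new data, and on the same assumptions the stated population can support the interaction.

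**What to change.** For each outcome compared across birth groups, and for each province, fit one model with a birth group by stratum interaction for each CIMD dimension used (for example ethnocultural composition and economic dependency). Fix one covariate set for all strata, without repeating the best-subset search within each. Report the interaction contrast with its 95% confidence interval.

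- **Binary outcomes:** beside the odds ratios, report standardised rates by birth group and stratum, and the between-stratum difference in risk differences.
- **Length of stay:** report the difference in mean differences.
- **COVID-19 vaccination:** a contrast with 2019 does not apply. Interact the stratum with the comparisons of Hypothesis 1.2 (pregnant v matched females) and Hypothesis 1.3 (Tdap v no Tdap, Ontario only).

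The cost is one more table and a little programming, since the standardised rates come from the same fit. Intervals for the interaction contrasts will be wider than those within a stratum, by a factor of about √2 = 1.41 for two strata of equal size and similar rates.

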### Qualitative design and methods

This strand uses a qualitative descriptive approach [62–64] which is most suitable for integrating with quantative analytic outputs, since both rely on post-positivist epistemology. Qualitative description is a low-inference applied health research methodology which instructs analysts to stay close to the explicit meaning of participants, rather than progressing to abstraction or interpretation.

#### Participants

Eligible participants are people aged 18 or over who gave birth to a live baby in Ontario or BC between May 2020 and December 2021. Participants must be comfortable completing an interview in English.

#### Sampling and recruitment

We will sample those who gave birth from May 1, 2020-Dec 1, 2021 to balance concerns of recall with information about different pandemic contexts. Guidance from one co-investigator with lived experience suggests that the complexity of health decision-making during the pandemic enhanced memory of this experience. We will use purposive sampling strategies, beginning with maximum variation to enroll an initial sample that represents diversity in age, SES, parity, race, geography, and occupational exposure to COVID-19. Preliminary analysis will suggest sampling strategies for future participants likely to yield analytically relevant findings. We will use a multi-pronged recruitment strategy, including posting advertisements online, in clinics and public parenting spaces. These advertisements will direct potential participants to an online or paper consent form which will explain the study and ask for socio-demographic information to be used for purposive sampling [65].

#### Sample size

We anticipate requiring 60–75 interview participants to reach sufficient information power that ensures our findings are credible and trustworthy [66]. This sample will be split between Ontario (~2/3) and BC (~1/3) to reflect the population differences between the provinces. This determination was made based on the heterogeneity of the sample, the three-pronged aim of the study, the use of established theory and the anticipated medium quality of dialogue [66].

#### Interview guide development

The interview guide was developed iteratively, with input from co-investigators who brought clinical, research, and lived experience of pandemic pregnancy. It was piloted and refined with three individuals who gave birth during the pandemic. The interview guide starts with a discussion of pandemic circumstances (family, housing, employment) and then elicits self-perceived risk of COVID-19 infection, complications, and long-term ramifications. Finally, the interviewer will inquire about decision-making processes relevant to the three topics of focus for this investigation (vaccination, prenatal care, mental health and social support).

#### Data collection

Each enrolled participant will participate in one individual, semi-structured interview. The interviews will be conducted by telephone, Zoom, or in-person as participant preferences and geographical restrictions allow. Pilot data collection indicates that the interviews will last between 30–60 minutes. Interviews will be audio-recorded and transcribed verbatim.

#### Qualitative analyses

Multiple analysts, including those with lived experience, will participate in conventional (inductive) content analysis [67, 68], using a staged process of coding adapted from Grounded Theory [69]. Analysis will focus on each theme separately, in conjunction with initial interview data about circumstances and risk perception. A multi-site qualitative analytic approach will maintain the site-specific context in the interviews while still offering comparative opportunity by theme [70]. An audit trail will be maintained, comprising of memos from each stage of data collection and analysis. Findings will be triangulated between analysts, and participants. Resonance will be ensured by presenting emerging finding to a focus group of pregnant people.

### Data integration

Data integration will occur at two points: during design and during interpretation. The project was designed with an objective framework-based mixing approach to develop complementary approaches for each of the three prenatal care themes [71]. After independent data collection and analysis, we will integrate findings at the point of interpretation, using a joint display technique, to compare changes in health behaviours with qualitative data explaining those changes [72].

## Strengths and limitations

This study has several strengths. The large administrative datasets offer significant statistical power to investigate changes in health care use, stratified by markers of socioeconomic and ethnocultural status. The cross-provincial nature of our analysis allows the observation of consistency or change based on different healthcare policies, vaccine availability, medical care provision, and COVID-19 burden. The integration with qualitative data offers the potential for explaining observed differences. Our study team incorporates multiple individuals with lived experience of a pandemic pregnancy, and frontline clinicians who cared for pregnant people in both provinces during the pandemic.

This study has some limitations. Relying on administrative data hinders the ability to gather some data points of interest. For example, neither ICES or PopData have patient-level demographic data about race or socioeconomic status. Instead, we will rely on area-level data abstracted from the 2016 Canadian Census, operationalized through the CIMD. The administrative datasets exclude some births, such as those which took place outside of a hospital setting. Qualitative data will be gathered from people who gave birth between May 1, 2020 to Dec 1, 2021, which may introduce some challenges with recall and social desirability bias. However, our co-investigators with lived experience assure us that due to the unique and challenging nature of these decisions, they are able to recall their decision-making very clearly.

## Ethics & dissemination

Ethics approval was received from McMaster University via the Hamilton Integrated Research Ethics Board for the qualitative strand (14632) and for the BC portion of the quantitative strand (15100C). Approval for the project was also received from the University of British Columbia Behavioural Research Ethics Board (H22-01905). Ethics approval was waived by McMaster University for the portion of the quantitative strand using ICES data (September 22, 2022) because the use of ICES data in this project is authorized under section 45 of Ontario’s Personal Health Information Protection Act (PHIPA) and does not require review by a Research Ethics Board.

This research will yield understanding about how a global pandemic and self-perceived risk influences health decision-making, which may inform health promotion initiatives through clinical counselling, public health communication and resource allocation, and policy development. Findings will be disseminated through peer-review manuscripts, at academic conferences, through clinical briefing notes and patient-facing materials.
